#### ***Patient outcome measures***

A number of patient outcomes will be measured: postoperative infectious complications, cardiovascular complications, and the length of acute hospital stay. In addition functional mobility at days 1 to 3 will be assessed using a cumulated ambulation score. Transfusion-related costs (consumables and nursing time) will be determined, and overall acute healthcare costs will be estimated from length of stay, investigations and drug costs.

### Study design

This is a prospective, single-centre, randomized, parallel group controlled trial conducted at the Queen’s Medical Centre campus of Nottingham University Hospitals, Nottingham, UK. Study recruitment commenced in July 2012 when the first patient was randomized. Recruitment is expected to take 24 months.

### Randomization and blinding

Randomization (on a one-to-one allocation basis) is via a password-protected web-based randomization service provided by the Clinical Trials Support Unit and the sequence is not revealed until datalock. Participants are randomized within 24 hours of admission, either before or after surgery.

The treating team, research nurse collecting data and research team analyzing data will be blinded to treatment allocation. The laboratory will be blinded to treatment allocation. The patient and ward nursing staff will not be blinded, for practical reasons (Venofer is a dark brown, aqueous solution). There is no placebo.

Postoperative data collection is by a research nurse blinded to treatment allocation. The decision that a patient is medically fit for discharge is made by the multiprofessional team, when all are satisfied that the participant has no ongoing needs for acute hospital care. This team is blinded to participant allocation.

### Selection and withdrawal of participants

#### ***Recruitment***

Participants are identified by their presence on surgical lists and are recruited from the trauma wards. The investigator informs the participant or the participant’s nominated representative (other individual or other body with appropriate jurisdiction), of all aspects pertaining to participation in the study. Active participation in the study is for the first seven days of hospital admission. The study intervention is complete after the third day (administration of i.v. iron) with daily blood tests until day 7. The medical notes are reviewed following hospital discharge for in-hospital complications and medication use.

Participants are informed that entry into the trial is voluntary and that they are free to withdraw at any time without effect on subsequent care. Data on time to discharge and postoperative mortality are collected routinely and separately from this study. These outcome data are therefore available for all randomized participants.

Patients who are unable to provide consent for themselves are not included in this study, owing to its pilot nature and the off-label use of intravenous iron.

Patients for whom language may be a barrier are eligible for inclusion to the study using standard interpreting services. In practice, this is a very small proportion of the total older population in the study centre.

### Inclusion criteria

Patients listed for or having undergone surgical repair of fractured neck of femur, who are aged 70 years or over and are admitted directly to the study centre through the emergency department will be included.

### Exclusion criteria

Participants will be excluded if they have had an undisplaced intracapsular fracture (as this requires a very low transfusion rate), or if there are any of the following contra-indications to intravenous iron therapy:

• Severe infection on admission.

• Liver disease.

• Known sensitivity to intravenous iron.

Participants taking iron orally will be excluded, as the simultaneous use of oral iron is prohibited in accordance with the licensing of Venofer (although taking oral iron prior to admission is not).

Participants will also be excluded if they are currently taking clopidogrel or ticlopidine (local practice is not to delay surgery for patients taking clopidogrel or ticlopidine, but they are at increased risk of bleeding in the intra-operative and perioperative period); aspirin is not an exclusion medication. (UK doses (75 mg or 150 mg) are not associated with increased surgical bleeding).

### Informed consent

The capacity for providing consent is assessed routinely by the orthopaedic team, who decide whether the patient is competent to provide consent for the surgical procedure. If the orthopaedic team deem the patient unable to consent to their surgery, then the patient will be deemed incapable of consenting to enter the study. A member of the research team also performs an additional check of the participant’s ability to provide consent, immediately prior to starting the study. All members of the research team are trained at obtaining consent in accordance with guidance for good clinical practice [30].

### Study intervention

#### ***Investigation medical product administration***

Patients allocated to the investigation medical product will receive 200 mg iron sucrose (Venofer) on three separate occasions. T1 will be day 1 (within 24 hours of admission); T2 will be day 1 after the operation, or the second morning following admission if the patient has not yet gone to theatre; T3 will be day 2 after the operation, or the third morning following admission if the patient has not yet gone to theatre.

Administration of intravenous iron will be in accordance with manufacturer’s recommendations. 10 ml Venofer (200 mg iron) will be diluted in 100 mls 0.9% sodium chloride for injections (to give a final concentration of 2 mg/ml).

On the first occasion, the first 25 mg of iron (i.e. 12.5 ml of solution) will be infused as a test dose over a period of 15 minutes. If no adverse reactions occur during this time then the remaining portion of the infusion will be given at an infusion rate of 100 mls/hour.

Oral iron is prohibited for at least 5 days following administration of intravenous iron. Given the negative results of a recent study of oral iron in hip fracture [13], oral iron will not be permitted for any study participants until day 10.

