**Methods/Design:**

This is a single-centre randomized controlled parallel group trial, in a British university hospital.Randomization is achieved using a website and computer-generated concealed tables. Participants are 80 patients 70 years or over with acute hip fracture undergoing operative repair. The intervention group receive three daily infusions of 200 mg iron sucrose, starting within 24 hours of admission. The control group receive standard hospital care at the discretion of the clinical team. Red cell transfusions for each group are given in accordance with standard clinical triggers. The primary outcome is an increase in mean reticulocyte count in the intervention group at day 7. Secondary outcome measures include haemoglobin concentrations, early and late transfusion rates, infectious and cardiovascular complications, mobility and 30-day mortality.

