## Methods/Design

### Study objectives

#### ***Primary aims***

To investigate whether intravenous iron given as three 200 mg doses over three days in patients with hip fracture causes an increase in reticulocyte count in the early postoperative period;

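### The dosing schedule puts doses 1 and 2 on the same date when surgery is on the day of admission and the first dose is given the next day (minor)

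*Protocol article*

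**What the plan says.** The schedule is in the protocol article under *Investigation medical product administration*. Patients in the iron arm receive "200 mg iron sucrose (Venofer) on three separate occasions". The three occasions have different anchors:

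- Dose 1: "T1 will be day 1 (within 24 hours of admission".
- Dose 2: "T2 will be day 1 after the operation, or the second morning following admission if the patient has not yet gone to theatre".
- Dose 3: "T3 will be day 2 after the operation, or the third morning following admission if the patient has not yet gone to theatre".

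Elsewhere the course is described as daily and lasting three days. The abstract (Methods/Design) says "The intervention group receive three daily infusions of 200 mg iron sucrose, starting within 24 hours of admission". The primary aim refers to "intravenous iron given as three 200 mg doses over three days". *Recruitment* says "The study intervention is complete after the third day (administration of i.v. iron) with daily blood tests until day 7".

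Two other sections allow the first dose to come after surgery. *Randomization and blinding* permits randomisation on either side of the operation, and *Inclusion criteria* admits patients whose repair has already been done.

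**The concern.** Dose 1 is tied to admission. Once surgery has been done, doses 2 and 3 are tied to the operation. Nothing ties dose 2 to dose 1, and no minimum interval is stated. If dose 1 is given after the operation, the two clocks can coincide.

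For such a patient the article gives two incompatible instructions. Staff who follow the dated schedule give two 200 mg infusions on one day. Staff who follow the abstract and the aim give one. What is at stake is a clear and consistently delivered regimen.

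**Working it through.** **Inputs.** Count the calendar date of admission as 0. Dose 1 falls on date 0 or 1, because it is given within 24 hours. For a patient who has had surgery, dose 2 is due on the operation date + 1 and dose 3 on the operation date + 2 (*Investigation medical product administration*). *Standard care* describes surgery within 36 hours, so surgery on date 0 is possible. I read day 1 after the operation in the usual way, as the next calendar date.

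**All cases with dose 1 after surgery.** The operation date cannot be later than the date of dose 1, so there are three combinations:

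| Surgery date | Dose 1 | Dose 2 (surgery + 1) | Dose 3 (surgery + 2) | Matches one dose a day for three days? |
|---|---|---|---|---|
| 0 | 0 | 1 | 2 | yes |
| 1 | 1 | 2 | 3 | yes |
| 0 | 1 | 1 | 2 | no |

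The stated course is reproduced in the first two rows. In the third row, 2 × 200 = 400 mg falls on date 1, and all 600 mg falls within two dates.

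**Example.** Admission is Monday 10:00, surgery Monday 18:00, and dose 1 Tuesday 09:00, which is hour 23. Tuesday is also the first day after the operation, so dose 2 is due on Tuesday and dose 3 on Wednesday.

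**Does another clause move dose 2?** The second-morning alternative covers only patients who have not yet gone to theatre. It does not apply here, whichever date that morning is taken to mean.

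**How often?** The article gives no distribution of dose or surgery times, so these are assumptions: admission uniform over the clock, dose 1 uniform over 0–24 h after admission, and surgery independent of dose 1 and uniform over one of three ranges. The simulation used 4,000,000 draws before the daytime limits (08:00–20:00). It gives the share of treated patients with doses 1 and 2 on one date:

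| Surgery after admission | No daytime limit | Surgery 08–20 | Dose 1 08–20 | Both 08–20 |
|---|---|---|---|---|
| 0–36 h | 11.1% | 12.0% | 6.5% | 5.6% |
| 12–36 h | 2.1% | 1.2% | 0.2% | 0.0% |
| 0–96 h | 4.2% | 4.5% | 2.4% | 2.1% |

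With both limits, the numbers in an arm of 40 are 0.056 × 40 = 2.2, 0, and 0.021 × 40 = 0.8. The full table spans 0 to 12%, and 0.12 × 40 = 4.8.

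The zero can be checked by hand. Surgery on date 0 at least 12 h after admission and before 20:00 needs admission before 08:00. Dose 1 on date 1 from 08:00 and within 24 h needs admission at or after 08:00. Both cannot hold.

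**The case against.** The strongest reply is that the regimen is already clear. The abstract says daily, the aim says three days, the schedule itself speaks of separate occasions, and "Administration of intravenous iron will be in accordance with" the manufacturer's recommendations. Sensible staff would space the doses, and a condensed article may leave minimum intervals to the full protocol.

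Part of this stands. Staff probably would space the doses, and an unstated interval alone would be no finding. But the article does fix dates, and for this patient they conflict with its own description of the course. Separate occasions need not be separate dates. The manufacturer's recommendations are not shown, so they cannot be used to settle the matter. No clause names another date for dose 2.

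Four stronger readings are tempting, and the article does not support them:

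- *A demonstrated safety problem.* A reader might infer that 400 mg in one day is harmful to frail older patients. The article gives no daily maximum and no evidence of such harm.
- *A threat to the result.* The total dose is still 600 mg, completed before the day 7 endpoint. Only timing within the iron arm changes, so the between-arm comparison is not affected.
- *A failure in one third of patients.* One of three date combinations fails, but combinations are not patients, and everyone first dosed before surgery is left out of that count.
- *A course that also runs too long.* Dose 1 on date 0 with surgery on date 1 gives dates 0, 2, 3 if the second morning is date 2. That is not strictly daily, but it is still three doses on three dosing days. It is a loose description, and a separate clerical matter.

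**Conclusion.** The point holds as a minor inconsistency. The schedule as written gives dates 1, 1, 2 for one permitted sequence of events, against the once-daily, three-day course stated in the abstract and the primary aim. This conditional result needs only the usual calendar meaning of a day after the operation.

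The frequency is much less certain. With surgery and dose 1 both limited to daytime, it is about 0 to 6% of treated patients, or 0 to 2 of 40. The upper figure comes from surgery spread evenly over 0–36 h. The 0–96 h range has a median of 48 h, in line with the UK figure in *Background*, and gives about 2%, or 1 of 40. The 12% extreme requires first doses at any hour of the night. All of these figures treat dose and surgery times as independent, for which the article offers no support either way.

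**What to change.** Add to *Investigation medical product administration*:

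> When T1 is given after surgery, T2 and T3 are given on the first and second calendar days after T1; no two doses are given on the same calendar day.

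For patients first dosed after surgery, the three date patterns become 0, 1, 2; 1, 2, 3; and 1, 2, 3. Only the faulty case changes. Patients first dosed before surgery keep their present rule, apart from the general bar on two doses on one date.

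The cost is one sentence in a minor amendment and a matching line on the drug chart, with no new visits, data or analysis. Optionally, the abstract, the primary aim and *Recruitment* could note that the three doses may span more than three calendar days when the first is given before surgery. That is clerical and not needed to resolve this point.

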#### ***Concomitant medication***

Analgesia will be provided in accordance with normal practice at the study centre. Nonsteroidal anti-inflammatory drugs are not prescribed routinely to this group of patients, and will be prohibited for patients in the study. Other medication will be prescribed by the attending medical staff as appropriate for each individual.

#### ***Concomitant treatments***

Physiotherapy, surgery and anaesthesia will be administered in accordance with normal clinical practice during the trial.

#### ***Laboratory analyses***

Blood samples will be taken from the participants on admission, and once each on days 1 to 7 following admission. Where possible, these blood samples will be taken at the same time as clinically required samples, to reduce the participants’ discomfort. Analysis will be carried out in the hospital’s haematology laboratory using standard techniques. This laboratory is certified in accordance with National Health Service standards, and undergoes its own quality assurance programme. Samples will be destroyed in accordance with normal procedures once analyzed, in accordance with the UK Human Tissue Act, 2006.

### Standard care

Standard care will be identical in both groups; only the administration of interventional medical product will differ.

All patients are admitted to dedicated trauma wards and cared for in accordance with UK ‘Best Practice Tariff’ [29]. This includes assessment by orthogeriatricians; operation within 36 hours of admission; and assessment of bone health and falls. All patients are cared for under a hip fracture care pathway, which involves rapid assessment and admission from the emergency department; intravenous crystalloid infusions from the time of admission and multiprofessional care and discharge planning. Operations are performed in dedicated trauma theatres by consultants in anaesthesia and orthopaedic trauma or senior trainees. The Queen’s Medical Centre has undertaken continuous, systematic audit of its hip fracture care since 2011 [4,11,31].

### Transfusion triggers

Perioperative transfusion will be at the discretion of the attending anaesthetist. Transfusion following return to the ward will be at the discretion of the ward team. Indications for transfusion are, in order of clinical priority:

• Ongoing blood loss with hypovolaemia;

• Symptomatic anaemia: anaemia with haemoglobin concentration < 10 g/dl associated with persistent hypotension, angina, heart failure or cerebral dysfunction;

• Asymptomatic anaemia with haemoglobin concentration < 8 g/dl;

• Relative anaemia ([Hb] significantly less than normal for the patient) and poor functional recovery.

### Cost analysis

Data on the cost of treatment will be calculated from drug use, investigations (diagnostic imaging, electrocardiography, blood testing) and the clinical record. This includes standardized costs for physiotherapy, occupational therapy and discharge planning. The cost of additional monitoring required for each patient will also be taken into consideration. Data will be presented in terms of total nonoperative costs, costs per day and excess costs attributable to treatment group.

### Statistics

Data will be analyzed by the research team in conjunction with a medical statistician, using the latest version of SPSS software. There will be no interim analysis.

The primary outcome measure, difference in mean reticulocyte count between groups in the full analysis set will be analyzed using unpaired *t* tests or Mann-Witney tests as appropriate. Differences between groups in maximal change in [Hb], serum transferrin concentration, postoperative mobility, number of units transfused and estimated costs will similarly be analyzed.

Risk ratios will be described for categorical data: the number of patients in each group with cardiovascular or infective complications; and the number of patients requiring transfusion. Descriptive statistics will be used to summarise length of stay and 30-day mortality.

Prespecified subgroup analysis will be undertaken according to admission haemoglobin concentrations ([Hb] <12 or >12 g/dl) and fracture type (sub-trochanteric, extracapsular, intracapsular, pathological).

In addition to the calculated values, confidence intervals and odds- ratios will be presented when appropriate. All clinical information including all adverse events will be presented in full. All secondary analyses will be interpreted with caution as the sample size calculation is based on the primary outcomes only. However, the level of power associated with secondary results will be investigated.

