### Sample size and justification

We propose to study a convenient sample size, with 40 participants in each group. Groups of 35 participants each would provide a statistical power of 80% for finding an absolute difference in maximum reticulocyte count of 1%, assuming a standard deviation of approximately 1.6%. This would also provide a statistical power of 80% for finding a difference in serum transferrin receptor concentration of 0.33 mg/dl. This is a conservative estimate of effect size; Garcia-Erce et al. [25] found differences of 1.75% and 0.4 mg/dl respectively. The extra ten patients are included to account for drop-outs.

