### Definition of datasets analyzed

The safety set will comprise all randomized participants who receive at least one dose of the study drug or are randomized to standard care. The full analysis set will comprise all randomized participants for whom at least initial and day 7 reticulocyte counts are available. The per-protocol set will comprise all participants in the full analysis set who are deemed to have no major protocol violations that could interfere with the objectives of the study. Safety summaries will be performed on the safety set.

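### The primary test makes no use of the admission reticulocyte count that every analysed patient must have; one prespecified ANCOVA would be more efficient, but reaches the stated 80% power only if the baseline correlation is about 0.4 or more

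*Protocol article*

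**What the plan says.** - **Test.** Statistics: "The primary outcome measure, difference in mean reticulocyte count between groups in the full analysis set will be analyzed using unpaired". A t test is one option and Mann-Whitney the other, and the only guide to the choice is this wording: "tests or Mann-Witney tests as appropriate". The section names no covariate and no rule for choosing the test. For haemoglobin it specifies a change measure; for reticulocytes it does not.
- **Sampling.** Laboratory analyses: "Blood samples will be taken from the participants on admission, and once each on days 1 to 7 following admission".
- **Analysis set.** Definition of datasets analyzed: "The full analysis set will comprise all randomized participants for whom at least initial and day 7 reticulocyte counts are available".
- **Outcome.** The Discussion part of the Abstract describes the measure as a change in reticulocyte count. The main Discussion describes an absolute difference, with day 7 as the primary time point.
- **Size.** Sample size and justification: "We propose to study a convenient sample size, with 40 participants in each group", and "Groups of 35 participants each would provide a statistical power of 80% for finding an absolute difference in maximum reticulocyte count of 1" percentage point, "assuming a standard deviation of approximately 1.6" percentage points.

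**The concern.** A patient without an admission count is dropped from the primary analysis, yet the stated test makes no use of that count. The value is on hand for every analysed patient, so adjusting for it needs no extra blood sample and no extra patient.

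The open choice of test matters separately. The outcome is a difference in means and the trial is sized on a mean difference of 1 percentage point. A t test matches that target; a Mann-Whitney test does not estimate it. The pilot is meant to supply the information for designing a full-scale trial, and that calls for a mean difference with its confidence interval and a standard deviation.

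At stake is precision in a small trial whose power, on its own inputs, appears to be below the stated figure.

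**Working it through.** **Inputs from Sample size and justification:** difference 1, standard deviation 1.6, 35 evaluable per arm (40 recruited), stated power 80%.

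**Assumptions, because the article does not state them:** two-sided alpha 0.05; 1.6 is the raw standard deviation, neither a change-score nor a residual one; and 1.6 applies to the day 7 count, although the article attaches it to the maximum count. The baseline-to-day-7 correlation r is not given, so a range is shown.

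**1. The plan's own figure.** Standard error = 1.6 × √(2/35) = 0.3825. Noncentrality = 1 / 0.3825 = 2.615. Normal approximation: Φ(2.615 − 1.960) = Φ(0.655) = 74.4%. Noncentral t with 68 degrees of freedom: 73.2%. The stated 80% is not reproduced. It would need 41 per arm (42 by the t calculation), or a standard deviation near 1.48 to 1.50 at 35 per arm. With all 40 per arm evaluable, power is 79.8% (78.8% by t). With one-sided 0.05, power at 35 per arm would be 83.4% (82.7% by t).

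**2. Mann-Whitney option.** Under normality, with relative efficiency 0.955, power at 35 per arm is about 72.4% (normal approximation).

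**3. ANCOVA on admission count.** Residual standard deviation = 1.6 × √(1 − r²), with one further degree of freedom used (67 at 35 per arm).

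| Assumed r | Residual SD | 35/arm, normal | 35/arm, t | 40/arm, t |
|---|---|---|---|---|
| 0 | 1.600 | 74.4% | 73.1% | 78.8% |
| 0.2 | 1.568 | 76.1% | 74.9% | 80.4% |
| 0.3 | 1.526 | 78.3% | 77.1% | 82.5% |
| 0.4 | 1.466 | 81.4% | 80.3% | 85.4% |
| 0.5 | 1.386 | 85.5% | 84.5% | 89.0% |

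**4. Correlation needed for 80% at 35 per arm.** The unadjusted requirement is 2 × [1.6 × (1.960 + 0.842)]² = 40.19 per arm. Setting 40.19 × (1 − r²) = 35 gives r = √(1 − 35/40.19) = 0.36. The t calculation gives 0.39.

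**5. Cost when the baseline is uninformative.** At r = 0, power at 35 per arm moves from 73.16% to 73.14%, about 0.02 points.

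**6. Change score as the alternative.** With equal standard deviations at the two times, the variance of a change is 2(1 − r) × 1.6². This is below the raw variance only if r exceeds 0.5. ANCOVA does at least as well as either analysis, apart from the one degree of freedom.

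**7. Type I error of the open choice.** Null simulation, 35 per arm, 10,000 runs for each of a normal, a lognormal and a gamma shape: choosing the test by a Shapiro normality pre-test gave 4.6% to 5.1%. Reporting the smaller of the two p-values gave 6.0% to 6.7%.

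**The case against.** An unadjusted comparison in a randomized trial is valid. A chance difference in admission counts is random error that the standard error already reflects; it is not bias. This stands, so the recommendation concerns efficiency and clarity only.

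A reader might infer that the open choice of test inflates the false-positive rate. The simulated 6.0% to 6.7% comes from taking the better of two p-values, which the article does not describe. The ordinary reading is a choice by distribution, and a pre-test rule of that kind stays near 5%.

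A reader might also infer that ANCOVA simply restores the missing power. The article gives no correlation, and surgery, blood loss, transfusion and the drug itself can all fall between the two samples. A value of 0.2 cannot be ruled out, and power would then be about 75%. The shortfall also depends on two-sided testing and on losing all ten extra patients. The article calls its effect size conservative against a cited 1.75; at that difference, power with 35 per arm exceeds 99%.

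The Statistics section does not itself say that raw day 7 values are compared, and the Abstract's mention of change, with the required initial count, could fit a change analysis. This stands in part: the role of the baseline is unsettled, which is itself a reason to name the model.

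Finally, covariates are often left to an analysis plan, and this is a condensed article. But the article does name its primary method, so the point rests on what it states and not on what it omits.

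**Conclusion.** The point holds as an efficiency recommendation that should be adopted. The stated primary test makes no use of a baseline that the analysis set guarantees, and it leaves open an option that does not estimate the quantity on which the trial is sized. Under the assumptions listed, ANCOVA raises power at 35 per arm from 73% to between 75% and 85% for correlations of 0.2 to 0.5, at negligible cost if the correlation is zero.

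It cannot be said that ANCOVA recovers the stated 80% outright: that needs a correlation of about 0.4 or more (0.36 by the normal approximation, 0.39 by t) and 1.6 as the raw standard deviation, neither of which is documented. Nor does the article support a claim of bias or of materially inflated type I error. Two matters lie outside this remedy: the sample size refers to the maximum count while the primary time point is day 7, and patients without a day 7 count are excluded from the analysis set.

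**What to change.** Before datalock, name one primary analysis: ANCOVA of the day 7 reticulocyte count on arm and admission reticulocyte count, in percentage points, reporting the adjusted mean difference with its 95% confidence interval. State that Mann-Whitney is a sensitivity analysis only. Align the Abstract's reference to change with this definition. Admission haemoglobin and fracture type are optional further covariates; if used, they and their coding should be fixed at the same time. The power figures above do not rely on them. Reporting the observed baseline-to-day-7 correlation and the residual standard deviation would help the design of the full-scale trial.

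Cost: a change of wording and one degree of freedom for the admission count, with a few more if the optional covariates are added. No extra patients or samples are needed, and the model runs in the planned SPSS software.

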
Intravenous iron therapy is relatively inexpensive; 200 mg of iron sucrose costs around £15. Administration costs for i.v. iron are likely to be similar to blood transfusion, in terms of consumables and nursing time. Even if the only benefit of intravenous iron is to reduce transfusion rates, the potential cost savings are considerable. Potential benefits, such as a reduction in infectious complications, which are suggested by the current literature, would result in significant cost savings to the healthcare economy, as well as improved quality of care. The direct consumable costs are probably slightly in favour of i.v. iron. With an estimated i.v. iron cost of £43 and blood unit cost of £200, assuming that an average of two units are transfused when given, if i.v. iron reduces transfusion rates from 38% to 25%, the direct cost saving in transfusion-related costs is around £10 per patient. Unlike cost savings from length of stay, these are direct savings to the healthcare system that can be realised, as well as releasing a scarce resource for use elsewhere.

The current literature supports the hypothesis that i.v. iron might be an effective and safe treatment, reducing the need for blood transfusion following hip fracture. Given the differences between UK and Spanish hip fracture management, particularly regarding time to operation, it is unclear whether the promising results from the Spanish experience will be applicable to the UK hip fracture population. It is unknown at present whether i.v. iron would have sufficient erythropoietic effect in hip fracture patients to reduce transfusion rates in the early postoperative period.

A large randomized controlled trial of preoperative i.v. iron for patients with hip fracture may be appropriate. To inform appropriate design of such a trial, a pilot study evaluating the haematological effect of i.v. iron in this population is required.

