#### ***Haematological measures***

As haematopoietic indices, full blood count and serum transferrin receptor concentrations will be measured. These will be collected daily for 7 days following admission. In addition, the number of patients requiring blood transfusion during hospital admission and the transfusion index (units/patient) will be determined.

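### The plan lets estimated costs be compared by a Mann-Whitney test, although its cost questions concern mean cost per patient

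*Protocol article*

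**What the plan says.** The Statistics section allows an unpaired t test or "Mann-Witney tests as appropriate" for the primary outcome and gives no rule for choosing. It extends the same choice to several secondary outcomes: "number of units transfused and estimated costs will similarly be analyzed". No other method is named for comparing costs.

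The questions asked of the cost data are stated elsewhere:

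- Cost analysis: "Data will be presented in terms of total nonoperative costs, costs per day and excess costs attributable to treatment group".
- Background: an argument from average cost, concluding that "the direct cost saving in transfusion-related costs is around £10 per patient".
- Patient outcome measures: two cost quantities, namely transfusion-related costs (consumables and nursing time) and overall acute healthcare costs (length of stay, investigations and drugs).

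Units transfused also have a mean as their summary: "the transfusion index (units/patient) will be determined".

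**The concern.** An excess cost and a saving per patient are differences in arithmetic means. Only a mean can be multiplied up to a budget, as the Discussion implies when it sets a possible cost benefit against around 80,000 operations a year. Mann-Whitney compares ranks: it asks how often a patient in one arm costs more than a patient in the other, and ignores by how much.

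The two questions can have opposite answers here. Every iron patient carries a modest drug cost, while a minority in each arm carries a large blood cost. Iron can then be dearer for most pairs of patients and cheaper on average. On the Background's rates, 62% of controls and 75% of iron patients receive no blood, so transfusion cost piles up at one value. An analyst could reasonably regard such data as a case for the rank test. The cost result is meant to help judge whether a full-scale trial is worthwhile, and a significant result in the wrong direction would mislead that judgement.

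**Working it through.** **Inputs.** All but the last two come from the article.

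- Prices (Background): "With an estimated i.v. iron cost of £43 and blood unit cost of £200".
- Units (Background): "assuming that an average of two units are transfused when given". Only the average is given.
- Transfusion rates (Background): "if i.v. iron reduces transfusion rates from 38% to 25" per cent.
- Size (Sample size and justification): 40 per group, 35 after drop-outs.
- Assumed: two-sided 0.05, because the article states no level for this test.
- Assumed: any spread of units around two, and any SD of other patient-level costs. The article gives neither.

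**Step 1. Reproduce the plan's own saving.**

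- Control: 0.38 × 2 × £200 = £152.
- Iron: £43 + 0.25 × 2 × £200 = £143.
- Difference: £152 − £143 = £9, which agrees with the stated figure of around £10.

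**Step 2. What the ranks say on the same figures.** With exactly two units per transfused patient, control costs are £0 or £400 and iron costs are £43 or £443. An iron patient is dearer than any untransfused control (probability 0.62). An iron patient is dearer than a transfused control (0.38) only if also transfused (0.25). So P(iron patient dearer) = 0.62 + 0.38 × 0.25 = 0.715. The medians are £0 and £43.

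**Step 3. How often each test is significant.** All combinations of Binomial(n, 0.38) and Binomial(n, 0.25) transfused counts were enumerated. Mann-Whitney used the tie-corrected normal approximation.

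| Test | Per arm | Iron significantly dearer | Iron significantly cheaper |
|---|---|---|---|
| Mann-Whitney | 40 | 92.1% | about 0% |
| Mann-Whitney | 35 | 89.4% | about 0% |
| Unpaired t test | 40 | 1.4% | 4.2% |

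**Step 4. How far this carries.** These are simulations at 40 per arm of Mann-Whitney declaring iron significantly dearer.

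- Units varying around a mean of two (uniform 1 to 3, or 1 + Poisson(1)): about 82% and 81%.
- Two units fixed, with other patient-level costs added as normal variation of assumed SD:

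| Assumed SD of other costs | Iron significantly dearer |
|---|---|
| £20 | 79% |
| £30 | about 50% |
| £43 | about 24% |
| £60 | about 10% |
| £100 | about 3% |
| £200 to £2,000 | about 1% to 2.5% |

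Lognormal other costs with assumed means of £1,000 to £5,000 give 2.0% to 2.5%. A test with no effect to find would give 2.5% in each tail, so at these spreads no reversal is left.

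**Step 5. Nursing time.** Patient outcome measures counts nursing time in transfusion-related cost. The £43 has no evident room for it, since the Background prices 200 mg at around £15 and three doses come to £45. Suppose an assumed cost *a* falls on each infusion and each unit of blood. Iron adds 3*a* and saves (0.76 − 0.50)*a* = 0.26*a*, a net 2.74*a*. The £9 saving is gone once *a* exceeds 9 / 2.74, about £3.30. If *a* falls once per course, the net is (1 − 0.13)*a* = 0.87*a*, and the threshold is 9 / 0.87, about £10.30. Above the threshold, mean and ranks agree that iron is dearer.

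**Step 6. Units transfused.** No drug cost enters here. At 40 per arm with two units fixed, Mann-Whitney finds iron significantly lower in 23.4% of trials and higher in 0.06%. Ranks and mean point the same way.

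**The case against.** The strongest reply is that 92% belongs to a cost the trial may never analyse: iron and blood consumables only, with exactly two units for every transfused patient. The overall cost covers stay, investigations, drugs, therapy and monitoring. Every patient incurs it, so it does not pile up at zero, and Step 4 shows the reversal vanishing once such variation is realistic. For transfusion-related cost, a few pounds of nursing time per infusion remove the £9 saving itself. This stands, and it limits the figure to an illustration.

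Three further points stand in part.

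- Mann-Whitney is permitted, not required, and a medical statistician is involved. But the article names the two tests for this outcome without a rule for choosing, and in the illustration they give conflicting messages. That is more than a detail left to an unseen analysis plan.
- Excess costs will be presented, with confidence intervals where appropriate, so a rank p-value need not stand alone. Nothing says, however, that the interval will be for a difference in mean cost.
- Costs are secondary and are to be interpreted with caution. The reason given is that the sample size rests on the primary outcome. That does not correct a test aimed at the wrong quantity.

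A reader might infer that the trial's cost result will probably come out in the wrong direction, or that the analysis of units transfused has the same fault. The article supports neither inference: the first needs the narrow cost of Step 2, and Step 6 contradicts the second.

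**Conclusion.** The point holds in limited form. The plan allows estimated costs to be compared by a test that does not address the mean cost difference it sets out to report. That mismatch needs no assumption about the data.

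Its practical size depends on the cost measured. For iron plus blood alone, on the Background's figures, the rank test contradicts a £9 mean saving in about 92% of trials at 40 per arm (89% at 35, about 82% with units varying), assuming a two-sided 0.05 level. With other patient-level costs the reversal is about 24% at an assumed SD of £43 and 3% or less from £100. For total costs no reversal is expected, although the article gives no SD to confirm this; there the fault is only that the test has the wrong target. Units transfused are not affected by the reversal. Since costs are secondary, this does not touch the primary conclusion, but the correction is nearly free and worth making.

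**What to change.** In the Statistics section, take estimated costs out of the list of outcomes analysed like the primary one and add a sentence: for transfusion-related costs and for total costs, the treatment comparison is the difference in arithmetic means with a bootstrap 95% confidence interval, and the cost conclusion does not rest on a Mann-Whitney test. Units transfused need no change on account of this point. The price is one sentence and slightly more analysis work; no new data are needed.
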